**Treatment Assignment and/or Randomization**

If participants meet eligibility criteria and a signed consent form has been received from a parent/guardian, they may be contacted and scheduled for a baseline session. For participants aged 18 years, baseline sessions may be scheduled prior to obtaining consent (as consent will be obtained at baseline prior to administering any study procedures). For all participants, a member of the study team will discuss the consent/assent form with the participant, provide answers to any questions, and, if the participant is interested, a licensed clinician will obtain informed consent/assent. The participant will then be given a signed copy of the consent/assent form.

Once enrolled and after the baseline phase (EMA Phase 1; Baseline as Usual), participants will be scheduled for randomization, which will employ a 2-arm, within-subject, parallel group design to examine effects of short- and longer-term withdrawal across 8 weeks of cannabis abstinence on depression and SI. Participants will be randomized to 8 weeks of abstinence with contingency management (CB-Abst: n=100) or non-contingent monitoring with no abstinence requirement (CB-Mon: n=100) using a 1:1 ratio in blocks of 6. A subset of study staff who will administer surveys and questionnaires querying about mood and suicidality will be blind to group assignment. Randomization will be based on a computerized scheme developed by the study statistician. Randomization will be stratified by age (<=14 years old vs >=15 years old), sex (male vs female), and depression severity (mild/moderate vs. Moderately severe/severe). A key aspect of the approach is that the 8-week period is long enough to observe true changes due to cannabis discontinuation, separate from effects of cannabis withdrawal and residual cannabinoid exposure. Groups will complete 1-week of EMA in weeks 1 (EMA Phase 2; Randomized Withdrawal) and 8 (EMA Phase 3; Randomized Sustained Abstinence) of the randomized study period.

Individuals randomized to monitoring who incidentally stop using cannabis, or express an interest in discontinuing cannabis, will not be removed from the study. If desired, these individuals will be provided with substance use resources at the time of interest in cessation.

1. **STUDY PROCEDURES**

Study procedures are nearly identical to those used in IRB approved pilot protocol (#2021P002416).

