
**Multiple testing.** We will use the false recovery rate adjustment to control for multiple testing across the 6 negative affect measures separately for each hypothesis (Benjamini, 1995).

*Sleep & Circadian Rhythms (Exploratory).* Fitbits will be worn throughout the trial to assess changes in sleep. Sleep, circadian, and physical activity exploratory Fitbit metrics include: *Sleep duration*: mean and standard deviation [StD]) over the main sleep period, the day, and 24hrs; short (<6 hrs) and long (>9hrs) mean nocturnal sleep duration; *Sleep fragmentation*: Mean and StD of 7-day sleep efficiency and wake after sleep onset; *Sleep timing placement*: Mean sleep onset, offset, and mid-point; categorized also as advanced (sleep onset <0900) and delayed (sleep onset >0200); *Sleep timing variability:* Across-day StD of sleep onset, inter-and intra-day stability; sleep offset, and sleep mid-point; relative activity- adjusted amplitude;192 *Physical activity:* Overall activity, time spent walking, in moderate and physical activity. Timing of maximal physical activity will be used in analyses of rest-activity rhythm.

**Missing Data***.* Some data will inevitably be missing. We will explore patterns of missingness to determine if missingness is occurring at random (MAR) (i.e., unrelated to the value of the missing observation) or missing not at random (MNAR). For each analysis, we will use a variety of recommended strategies to address the issue of missing data (e.g., multiple imputation, maximum likelihood estimation) (Schafer & Graham, 2002). Consistency in findings across missing data methods will enhance our confidence in the findings. If findings are discrepant, we will assume that participants randomized to CB-Abst have resumed using cannabis, if they are lost to follow-up.

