**Protocol non-adherence.** Analyses involving phase 1 and/or phase 2 of EMA data collection, will only consider CB-Abst participants who have biochemically-validated CB abstinence for two months because the goal is to study the effect of abstinence on change in mood and SI. If fewer than expected CB-Abst abstain from CB use for the full two months, we will form Helmert contrasts: those in CB-Mon (a), CB-Abst who do not abstain (b), and CB-Abst who abstain (c). The 1^st^ Helmert contrast will compare a to b+c and will be the intent to treat comparison. The 2^nd^ contrast will compare b to c, which corresponds to the post hoc sensitivity analysis of interest. Similar considerations will be made if participants in CB-Mon incidentally discontinue CB use during the study.

**Power analysis and justification of recruitment targets for the confirmatory cohort.** The R package ‘EMAtools’ (version 0.1.3; Kleiman, 2017) was used to determine the power for the proposed analyses. Preliminary analyses from the exploratory study found effect size estimates for significant effects ranged from 0.19 to 0.44, and that 77% of participants completed all phases of the study, completing on average 76% of all prompts. Estimates of the power were therefore computed to detect a weak effect (a Cohen’s d of .2) based on linear multi-level models using the nesting structure for the proposed EMA analyses and an intra-class correlation of .09. Table 1 shows the breakdown of estimates power based on the hypothesis being tested under two scenarios: 1) an ideal scenario with the full proposed number of participants and responses, and 2) a realistic scenario where 77% of participants complete 76% of entries.

Table 1: Power estimates by hypothesis and attrition scenario (ideal versus worse-case)

| Hypothesis | N (%) for sample size | N (%) of completed entries | Power |
| --- | --- | --- | --- |
| 1.1 - 1.2 | 200 (100%) | 112 (100%) | 99% |
|  | 154 (77%) | 85 (76%) | 93% |
| 2.1 - 2.2 | 200 (100%) | 224 (100%) | 99% |
|  | 154 (77%) | 170 (76%) | 94% |

1. **Monitoring and Quality Assurance**

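### Agreement between missing-data methods is counted as support for the findings, but both methods named assume MAR, so agreement says little about informative dropout

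*Protocol*

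**What the plan says.** The Missing Data paragraph (protocol, Statistical Analysis) sets out four steps.

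1. Classify the mechanism: "We will explore patterns of missingness to determine if missingness is occurring at random (MAR") or not at random. The paragraph glosses MAR as missingness that does not depend on the missing value itself.
2. Apply several methods, with two given as examples: "e.g., multiple imputation, maximum likelihood estimation".
3. Read agreement as reassurance: "Consistency in findings across missing data methods will enhance our confidence in the findings".
4. Make a different assumption only on disagreement: "If findings are discrepant, we will assume that participants randomized to CB-Abst have resumed using cannabis, if they are lost to follow-up".

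The power section gives the expected loss, taken from the exploratory study: "77% of participants completed all phases of the study, completing on average 76% of all prompts". The protocol names no sensitivity analysis that lets the missing mood or SI scores depart from MAR.

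**The concern.** Step 1 asks something of the data that they cannot deliver. Patterns of missingness can argue against data missing completely at random. Whether missingness depends on the unseen score, given what was seen, turns on values nobody has.

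Step 3 then draws comfort from a comparison that is close to blind to the main threat. In standard form the two named methods rest on the same assumption and estimate the same quantity. If that assumption fails, both are wrong by about the same amount.

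The protocol gives reasons to take informative loss seriously. Hypothesis 2.1 predicts that mood and SI worsen in CB-Abst but not CB-Mon, which is an arm-specific reason to stop answering. The investigator may end participation on safety grounds. The safety-monitoring section lists retention and reasons for drop-out among data that may differ between groups for safety reasons.

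If the worst-off CB-Abst participants go missing, phase 3 negative affect in that arm is understated. Hypothesis 2.2 can then look true, and agreement between methods would be cited in its favour. That matters in a trial reporting on SI in adolescents.

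**Working it through.** **The plan's own figures.** The protocol states no agreement rate between methods. Its loss figures reproduce: 200 x 0.77 = 154 participants retained, so 46 (23%) do not complete all phases; 112 x 0.76 = 85.1 and 224 x 0.76 = 170.2 prompts, shown as 85 and 170.

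**Why the methods move together.** Let a fraction p of an arm be missing at phase 3, and let the missing scores be worse by d (in SD) than a MAR model predicts. Any MAR estimate of that arm's mean is then too favourable by p x d. With p = 0.23 and, for illustration, d = 0.5, this is 0.23 x 0.5 = 0.115 SD. The term is the same for maximum likelihood and for multiple imputation with the same variables, so it cancels from their difference. What remains is mainly imputation noise.

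**Simulation.** Inputs from the documents: 100 per arm ("using a 1:1 ratio in blocks of 6", N = 200), 23% missing, and the phase 3 versus phase 1 group-by-phase contrast. True effects of 0, -0.2 and -0.4 SD were chosen in light of the pilot ("effect size estimates for significant effects ranged from 0.19 to 0.44"). Inputs assumed: three normal phase-level scores per person, between-phase correlation 0.3, 0.5 or 0.7, all loss at phase 3, and the dropout mechanism (MAR on the phase 2 score, or dependent on the unseen phase 3 score in CB-Abst only). Multiple imputation used Bayesian regression, 20 imputations and Rubin's rules, with 1,500 runs per cell. Agreement means the same verdict at two-sided 0.05.

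Correlation 0.5, true effect zero:

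| Dropout at phase 3 | Same verdict | Mean absolute ML-MI difference (SD) | Bias (SD) | p < 0.05, ML / MI |
|---|---|---|---|---|
| MAR, 23% per arm | 99.1% | 0.012 | -0.002 | 5.1% / 5.1% |
| Informative, moderate, 23% per arm | 98.3% | 0.011 | -0.135 | 13.6% / 13.7% |
| Informative, strong, 23% per arm | 97.5% | 0.011 | -0.217 | 29.7% / 29.8% |
| Informative, strong, 36% vs 10% | 96.7% | 0.012 | -0.328 | 55.0% / 55.2% |

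Over all 36 combinations of correlation, effect and mechanism, agreement was 95.9-99.2% under MAR and 96.6-99.9% under informative dropout. At zero effect with 23% missing per arm, informative dropout gave bias from -0.09 to -0.27 SD.

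**A parameterised check.** This used correlation 0.6, zero effect, 2,000 trials and 20 imputations. Log-odds of CB-Abst dropout rose by 1.0 or 1.5 per SD of unseen phase 3 affect. Agreement was 98% and 96% (99% without informative dropout). Bias was -0.11 and -0.15 SD.

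**Where the figures move.**
- With 5 imputations, agreement was 93.0-97.9%; with 100 it was 98.6-99.2%.
- One auxiliary variable was given to multiple imputation only and assumed observed for everyone. Agreement was 97-99% without informative dropout. With slopes 1.0 / 1.5 it was 95% / 93% (auxiliary correlation 0.7) or 92% / 88% (0.8). With 35% vs 11% dropout it was 85% / 77% for those two correlations. Bias was reduced but not removed.
- With 12% missing per arm and slope 1.0, bias was -0.06 SD.

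**The case against.** **This is detail for the SAP.** The two methods follow an e.g., so the list is open, and an SAP not shown may add an MNAR method. That stands: the absence of such a method from the protocol is not in itself the fault. The fault is in two statements the protocol does make, on classifying the mechanism and on what consistency shows. Both would need correcting whatever the SAP adds.

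**The consistency sentence is soft.** A reader might infer that findings will be accepted whenever the methods agree. The text does not say so; it says confidence is enhanced. The point is therefore about false reassurance, not an acceptance rule.

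**High agreement is not built into the plan.** A reader might take the roughly 96-99% as a fact about this trial. It assumes both methods use the same variables, which the protocol does not fix. PHQ-9 is collected at every visit, and if only one method used it, agreement could fall, and fall further under informative dropout. This stands. Even so, a gap between methods would reflect the auxiliary variable's information and would not test for MNAR.

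**The simulated comparison is not the main Aim 2 analysis.** A reader might infer that the planned test of Hypothesis 2.2 has the inflated error rates in the table. The documents do not support that. The Aim 2 text and the Protocol non-adherence paragraph keep only CB-Abst participants with confirmed abstinence, so many who leave would be excluded rather than imputed. The simulation is closer to the first Helmert contrast, the intent-to-treat comparison. The 23% may also include losses in phase 1, before randomization, and no figure in the protocol shows differential dropout.

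**There is mitigation.** An optional exit interview with PHQ-9 is offered to participants who do not want to complete all procedures. It helps and belongs in the analysis, but it is voluntary and measures neither momentary mood nor SI on the EMA items.

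**Conclusion.** The point holds in a limited form. Observed patterns cannot establish MAR against MNAR. Agreement between the two named methods says little about informative dropout or non-response. The only alternative assumption is reached on disagreement, and it concerns cannabis use rather than the missing outcome.

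As to size, under the assumed mechanisms agreement stayed at roughly 96-99% whether or not dropout was informative, while bias went from about zero to about -0.1 to -0.3 SD. This rests on assumed dropout slopes, normal phase means in place of the planned zero-inflated beta model, identical variables in both methods, 20 imputations, and all 23% of loss falling after randomization. Agreement is lower with few imputations or unequal auxiliary information, and bias is smaller with less post-randomization loss. The direction of the argument does not depend on these choices; the percentages do.

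The change should be made, since the sentence can lend false support to an Aim 2 conclusion and the remedy is cheap.

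**What to change.** In the Missing Data paragraph:

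1. Replace the aim of deciding between MAR and MNAR with a description of missingness by arm and phase and of its observed predictors.
2. Delete the consistency sentence as a criterion of robustness.
3. State a main analysis under MAR, with visit-level PHQ-9, C-SSRS and Cannabis Withdrawal Scale scores as auxiliary variables, and exit-interview PHQ-9 where available. The three scales are already scheduled at every visit in both arms.
4. Always run, not only on disagreement, a pattern-mixture delta adjustment of the missing mood and SI scores. Vary delta separately by arm over a stated range (0 to 0.5 SD worse would be one choice). Apply it to the Aim 2 analyses, including the intent-to-treat Helmert contrast, and report the delta at which each Hypothesis 2.1 and 2.2 conclusion changes.

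The cost is new wording and one more sensitivity run per measure, with no new data collection. Some findings may have to be reported as fragile. The change does not address selection from restricting CB-Abst to confirmed abstainers, which is a separate issue.

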**Statistical models.** Separate analyses will be conducted for each negative affect measure. Statistical models will assume that a) data are a mixture of a non-zero continuous component and zeros, and b) the continuous component will follow a beta distribution (i.e., scores will be scaled to be between 0 and 1). Models will include 1) a participant-varying lag-1 autocorrelation term (to handle repeated measures) and 2) a participant-varying probability term governing the occurrence of zeros (to allow for individual differences). Additional covariates will include weekday (categorical, Monday-Sunday), time of day (categorical, 6:00-11:00, 11:00-16:00, 16:00-21:00), age (continuous), and gender (categorical). To test specific hypotheses, additional predictors will be included as needed for a) the beta regression, b) the residual variance term of the beta regression, and c) the probability term governing zeros.

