**Data analysis.**

**Aim 1: To test if negative mood and SI are temporarily relieved and stabilized through acute cannabis use (i.e., negative reinforcement cycle).** We will only use phase 1 data, the 2-week baseline period in which all participants may use cannabis. *Hypothesis 1.1:* We hypothesize that negative affect measures for a) the current random prompt, and b) the prior random prompt (a lag-1 term) will predict 1) greater cannabis use independent of motivating reason (i.e., lower probability for the zero component of the model), and 2) higher scores for motivated cannabis use to improve negative mood. Negative affect measures will therefore be converted to z-scores for this analysis and included as predictors for both the zero and non-zero components of the model. *Hypothesis 1.2:* We hypothesize that the binary indicator for cannabis use in the last hour will predict lower, less variable scores for the negative affect measures. Therefore, the binary use indicator will be included as a predictor for the beta regression residual variance term as well. *Hypothesis 1.3 (exploratory):* There will be within-subject correlates (e.g., concurrent other substance use, social context of use) and between-subject factors (e.g., cannabis use and depression severity, history of suicidal behavior) that moderate relationships between acute cannabis use and negative affect.

**Aim 2: To test if negative mood and SI initially increase with the start of abstinence and then decrease in both mean levels and variability after cannabis wash-out.** We will use phase 1 – 3 data, including predictors for a) group differences (CB-Abst vs. CB-Mon), b) differences by phase (phase 3 vs. phase 1 and phase 2 vs. phase 1), and c) terms for the group by phase interactions. All terms will be included as predictors for the beta regression residual variance term as well. We will only include data for the CB-Abst group with confirmed abstinence for phases 2 – 3. *Hypothesis 2.1:* We hypothesize that CB-Abst will show higher mean negative affect scores and greater variability during phase 2 compared to phase 1, while CB-Mon will show no differences between phases. *Hypothesis 2.2:* We hypothesize that CB-Abst will show lower mean negative affect scores and less variability during phase 3 compared to phase 1, while CB-Mon will show no differences between phases.

**Exploratory analyses:** To further assess heterogeneity in suicidal ideation, we will conduct a set of

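### The fallback for discrepant missing-data results sets cannabis status, in CB-Abst only, and supplies no mood or SI score, so it cannot resolve the discrepancy

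*Protocol*

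**What the plan says.** Protocol, Statistical Analysis, Missing Data, takes three steps.

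- It sets out to classify the mechanism: "We will explore patterns of missingness to determine if missingness is occurring at random (MAR" and so on, as against MNAR.
- For each analysis, "we will use a variety of recommended strategies to address the issue of missing data (e.g., multiple imputation, maximum likelihood estimation" and similar. Agreement between methods is taken as reassurance.
- If they disagree: "If findings are discrepant, we will assume that participants randomized to CB-Abst have resumed using cannabis, if they are lost to follow-up".

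The outcomes that go missing are the six EMA measures of negative affect, SI and self-injury urges. Under Statistical models, "Separate analyses will be conducted for each negative affect measure".

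Two other paragraphs decide who enters Aim 2. The Aim 2 text says "We will only include data for the CB-Abst group with confirmed abstinence for phases 2 – 3". Protocol non-adherence says that the analyses it covers "will only consider CB-Abst participants who have biochemically-validated CB abstinence for two months". It then adds "If fewer than expected CB-Abst abstain from CB use for the full two months, we will form Helmert contrasts". In these contrasts a is CB-Mon, b is CB-Abst not abstaining and c is CB-Abst abstaining. The first contrast, a against b+c, is labelled intent to treat. No number is given for what is expected. The paragraph extends similar thinking to CB-Mon participants who stop using, but not to those who are lost.

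**The concern.** A fallback for disagreement between missing-data methods should say something about the unobserved outcome. This one makes a statement about drug use instead, for one arm, and only once the results are seen to differ. It comes into play exactly where missingness affects the answer, and it then gives the analyst no mood or SI value to work with.

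The one-arm rule also meets a one-arm inclusion filter. CB-Abst must show abstinence to be counted, and CB-Mon has no such test. If adolescents leave because mood worsens in withdrawal, they drop out of view in the arm where worsening is the hypothesis (2.1). The loss also flatters the later improvement in that arm (2.2). The bias therefore cannot be called conservative.

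**Working it through.** **1. What happens to a lost participant**

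| Participant and rule | Result | What the fallback adds |
|---|---|---|
| CB-Abst, two-month rule | Cannot show two months of validated abstinence, so already excluded | Nothing, unless imputed abstinence would have been accepted |
| CB-Abst, Aim 2 rule read phase by phase | Week 1 abstinence can be confirmed at V3-V5 (days 16, 19, 21), so phase 2 data may stay; phase 3 is absent | Excludes only where imputed abstinence or imputed phase 3 data would have been used |
| CB-Abst, Helmert contrasts | Falls in group b, stays in a against b+c | Classification only, no mood value |
| CB-Mon | No filter; observed prompts stay, missing phase 3 goes to imputation or likelihood | Not covered |

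**2. The trigger.** Multiple imputation and maximum likelihood under the same MAR model should roughly agree even when data are MNAR. Agreement therefore does not rule out MNAR. Disagreement, which the text does not define, does not show it.

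**3. MAR or MNAR.** The two differ in whether missingness depends on unobserved values once observed data are taken into account. Observed patterns cannot separate them. The protocol's gloss on MAR also leaves out the conditioning on observed data.

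**4. Size**

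Inputs: 100 per arm (Treatment Assignment and/or Randomization); 77% completing all phases in the exploratory study, d = 0.2 and ICC = 0.09 (Power analysis). The plan's Aim 2 attrition counts reproduce: 200 x 0.77 = 154, and 224 x 0.76 = 170.2, shown as 170.

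Let p be the fraction lost after randomisation and delta the dropout minus completer difference in mood change.

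- Whole-arm mean = completer mean + p x delta.
- Completers-only mean = completer mean.
- With dropout alike in both arms and CB-Mon dropouts fully represented, bias in CB-Abst minus CB-Mon = -p x delta.

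Taking p at its upper value, 1 - 0.77 = 0.23:

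| delta (SD) | 0.23 x delta |
|---|---|
| 0.2 | 0.05 |
| 0.4 | 0.09 |
| 0.8 | 0.18 |
| 0.87 | 0.20 |

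If CB-Mon dropouts carry only half their weight, these halve (0.046 at delta 0.4).

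A simulation with no true effect checks the direction. Its assumptions are person-level phase means correlated 0.6, 23% dropout in both arms driven by phase 1-to-2 worsening, CB-Abst completers only, and CB-Mon with all phase 2 data plus MAR regression for phase 3.

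| Dropout log-odds slope per SD | delta | Phase 2 bias | Phase 3 bias |
|---|---|---|---|
| 0 | 0.00 | 0.00 | 0.00 |
| 0.5 | 0.38 | -0.09 | -0.04 |
| 1.0 | 0.70 | -0.16 | -0.08 |
| 1.5 | 0.93 | -0.21 | -0.11 |

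The phase 2 column matches 0.23 x delta. When dropout follows the phase 2 level instead of the worsening, the same three slopes give about -0.05, -0.08 and -0.10 at phase 2 and about zero at phase 3. The mechanism matters as much as the rate.

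**5. Scale.** These are person-level SDs. If d = 0.2 is on the total SD (the protocol does not say), the between-person SD is the square root of 0.09 = 0.3 of it. Then delta 0.4 gives 0.23 x 0.4 x 0.3 = 0.028, and delta 0.8 gives 0.055.

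**The case against.** Four points deserve weight.

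- **The exclusion has another source.** The Aim 2 and non-adherence rules already remove anyone without validated abstinence. Deleting the fallback alone would leave the asymmetry in place. This stands, and the fix has to deal with the filter as well.
- **Abstinence status is also missing for a lost participant.** It decides analysis-set and Helmert membership, so some rule for it is needed, and resumed use has no meaning in CB-Mon, which has no abstinence requirement. This stands as a defence of the rule for classification. It does not make it an answer to discrepant mood results.
- **Mood is not left unhandled.** Imputation and likelihood come first, and the Helmert route keeps deemed resumers in an intent-to-treat contrast. Both are true. But that route opens only if abstinence falls short of an unstated expectation, and it supplies no mood values.
- **Methods detail may sit in the SAP.** Naming a primary method often does, and no stated analysis turns on the MAR or MNAR verdict. The point here is limited to what the protocol states: a fallback on the wrong variable and a claim that cannot be met.

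A reader might infer that the fallback itself deletes about 23 of 100 CB-Abst participants and shifts the result by a third or more of the planned effect: 0.23 x 0.3 = 0.069 and 0.23 x 0.5 = 0.115, or 35% and 58% of 0.2. The documents do not support that. The 77% is an all-phase rate that may include loss before randomisation, it is not split by arm, and the 0.3 to 0.5 is assumed on an unstated SD. On the between-person reading the same figures become 0.021 and 0.035, or 10% and 17%.

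**Conclusion.** The point holds in this form. The fallback assigns cannabis status, covers CB-Abst only and is triggered by the results, so it cannot resolve disagreement about missing mood or SI. With the confirmed-abstinence restriction, which does most of the work, CB-Abst dropouts are left out of the main Aim 2 comparison while CB-Mon dropouts' observed data remain. The conditional Helmert contrasts are the only stated route that keeps them.

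The bias is roughly p x delta: at most about 0.23 x delta for losses up to 23%, and zero if dropout is unrelated to mood. It would mask the rise in hypothesis 2.1 and, where dropout follows worsening, favour the fall in 2.2. Both p after randomisation and delta are assumptions, so no share of the planned effect should be quoted. The claim to determine MAR versus MNAR from patterns is wrong as stated. This should be changed, but it does not show that the trial's comparison fails.

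**What to change.** - Delete the assumption of resumed use as the response to discrepant outcome results. It may be kept only to classify abstinence status (group b).
- Delete the claim to determine MAR versus MNAR. Describe the missingness patterns and state MAR as an assumption.
- Name one primary approach for both arms: likelihood-based under MAR, using all observed prompts of randomised participants, with phase 1 mood and compliance in the model.
- Always report the a against b+c contrast, not only when abstinence is low. Keep the confirmed-abstinence analysis as a separate, labelled analysis. This changes the present filter, so the text should say so.
- Reconcile the two filter paragraphs: one refers to phases 2 and 3, the other to phases 1 and/or 2.
- Add a pre-specified delta-adjusted sensitivity analysis that shifts dropouts' unobserved mood, by arm, over a stated range (for example 0 to 0.5 SD, naming the SD) and reports where the conclusion changes.

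The cost is wording and one extra sensitivity analysis. No data collection changes.

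### Read literally, the protocol's non-adherence rule selects Aim 1's pre-randomisation data on later abstinence, and conflicts with the rule in the Aim 2 paragraph

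*Protocol*

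**What the plan says.** Two paragraphs of the protocol's Statistical Analysis section say whose data are used.

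- **Data analysis, Aim 1:** "We will only use phase 1 data, the 2-week baseline period in which all participants may use cannabis". No abstinence condition is attached.
- **Data analysis, Aim 2:** all three phases are used, with phase 1 as the reference. The restriction reads "We will only include data for the CB-Abst group with confirmed abstinence for phases 2 – 3".
- **Protocol non-adherence:** here the restriction is worded differently: "Analyses involving phase 1 and/or phase 2 of EMA data collection, will only consider CB-Abst participants who have biochemically-validated CB abstinence for two months". The reason given is "because the goal is to study the effect of abstinence on change in mood and SI".

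The section Treatment Assignment and/or Randomization fixes the order of events: "Once enrolled and after the baseline phase (EMA Phase 1; Baseline as Usual), participants will be scheduled for randomization". Phases 2 and 3 are weeks 1 and 8 after randomisation, with 100 participants planned per arm.

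The non-adherence paragraph adds a fallback. If abstinence is lower than expected, Helmert contrasts will compare CB-Mon with all of CB-Abst (labelled intent to treat), and CB-Abst abstainers with non-abstainers. No expected rate is given.

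Table 1 gives hypotheses 1.1 and 1.2 a sample of 200 in the ideal case and 154 after 77% completion.

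**The concern.** Aim 1 is an analysis involving phase 1, so the non-adherence rule covers it as worded. Arm and two-month abstinence are known only after every Aim 1 observation has been collected. Applying the rule would filter one arm's baseline data on a post-randomisation outcome and leave the other arm unfiltered. Ability to abstain may well be related to use severity, mood and coping use, which are close to what Aim 1 estimates.

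The rule also reaches hypothesis 2.1, which concerns the first week of withdrawal. A CB-Abst participant with verified abstinence in week 1 who lapses in, say, week 5 would lose the week-1 data.

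An analyst cannot follow both paragraphs as written. Both govern analyses of outcomes that the protocol calls primary. If the choice stays open, it could be made after the data are seen.

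**Working it through.** **1. The texts side by side**

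| Source | Phases named | Abstinence required |
|---|---|---|
| Data analysis, Aim 1 | 1 | none |
| Data analysis, Aim 2 | 2 and 3 | confirmed; duration not spelled out |
| Protocol non-adherence | 1 and/or 2 | two months, validated |
| Table 1, H1.1-1.2 | (Aim 1 data) | none; N = 200 or 154 |

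Phase 2 appears in both restriction rules. The conflict is that one rule adds phase 1 and does not name phase 3. The stated rationale, the effect of abstinence on change, can apply only to Aim 2, because phase 1 contains no assigned abstinence.

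**2. Table 1's Aim 1 power**

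Inputs from the power paragraph: d = 0.2, ICC = 0.09, N = 200, m = 112 entries. Two-sided alpha of 0.05 is assumed, as none is stated. The check uses a design-effect approximation, not the R package the protocol used.

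- Neff = N·m / (1 + (m − 1)·ICC) = 200 × 112 / (1 + 111 × 0.09) = 22,400 / 10.99 = 2,038
- Power = Φ(d·√Neff / 2 − 1.96) = Φ(4.515 − 1.96) = 99.5%, against 99% stated. The ideal row reproduces.

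The attrition row (154 participants, 85 entries) gives 97.4% by this formula, against 93% stated, so it does not reproduce. Nothing below depends on that row.

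**3. Aim 1 under the literal rule**

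Let q be the share of CB-Abst with two months of validated abstinence. The documents give no value; 40% to 80% is assumed. N retained = 100 + 100q.

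| q | N kept of 200 | Neff (m = 112) | Power |
|---|---|---|---|
| 80% | 180 | 1,834 | 99.0% |
| 50% | 150 | 1,529 | 97.4% |
| 40% | 140 | 1,427 | 96.5% |

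The loss is 10% to 30% of participants, and the cost in power is small. At a more pessimistic q of 25%, N = 125 and power is 94.6%.

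**4. Size of the selection effect**

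Suppose the Aim 1 association differs by δ between participants who would and would not abstain under contingency management. Assume randomisation gives both arms the same mix, and weight participants equally.

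- Full cohort: abstainer value + (1 − q)δ
- Literal rule: abstainer value + (1 − q)δ / (1 + q), because only CB-Mon still contributes non-abstainers
- Shift = −q(1 − q)δ / (1 + q)

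At q = 40% the shift is 0.24/1.4 = 0.17δ, and at q = 80% it is 0.16/1.8 = 0.09δ. The documents give no information on δ.

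**5. Hypothesis 2.1**

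Phase 2 runs from V2 (day 14) to V5 (day 21), and two months of abstinence runs to V12 (day 70). Entry of data from days 14 to 21 therefore depends on status about seven weeks later. If harder withdrawal makes lapse more likely, the retained group has milder withdrawal. That direction is plausible, but nothing in the documents establishes it.

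**The case against.** The strongest reply is that this is a wording slip: phases 2 and/or 3 were probably meant. The Aim 1 paragraph, the rationale and Table 1 all support that reading. A reader might infer that the investigators plan to cut Aim 1, but the documents do not show such a plan. What stands is that the text as written says otherwise and must be reconciled. That phases 2 and 3 were intended remains an inference.

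Other stronger readings also fail:

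- **Phase 3 is left unrestricted.** It is not named in the non-adherence rule, but every planned Aim 2 contrast uses phase 1 as reference and so falls under that rule. The Aim 2 paragraph also restricts phase 3 expressly. The omission has little practical effect.
- **The two rules contradict each other on hypothesis 2.1.** Confirmed abstinence for phases 2 and 3 can be read as abstinence across both, which is compatible with two months. On this hypothesis the point is mainly about conditioning on later status.
- **Withdrawal effects will be understated.** This is plausible only. Those excluded are also not simply the participants least able to stop, since dropout or missing samples can prevent validation too.
- **Aim 1 would be underpowered.** The calculation does not support this over the assumed range.

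The Helmert fallback is a partial safeguard, because its first contrast keeps all of CB-Abst. However, its trigger is not quantified and it addresses the arm comparison, so it does not settle who enters Aim 1.

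**Conclusion.** The concern holds. Read literally, the non-adherence rule conditions a pre-randomisation analysis of primary outcomes on later abstinence in one arm, and it conflicts with the Aim 2 paragraph, its own rationale and Table 1. It should be corrected before analysis.

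If it were applied, Aim 1 would keep 140 to 180 of 200 participants with about 96% to 99% power. This assumes 40% to 80% abstinence, full entries, the protocol's d and ICC, and two-sided 0.05. The main harm is selection, of a size that depends on an unknown difference between abstainers and non-abstainers. For hypothesis 2.1, dependence on week-8 status is a real weakness, but the direction of any bias is not established.

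**What to change.** Make two changes to the Statistical Analysis section.

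1. State that Aim 1 uses all participants with phase 1 data, whatever their later arm or abstinence.
2. Give the same Aim 2 rule in the Aim 2 and Protocol non-adherence paragraphs. Define abstinence for the abstainer analysis by phase: verified through week 1 (V3 to V5) for phase 2, and through week 8 (V12) for phase 3. Say whether a participant who fails the rule loses all records or only those of the affected phase.

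The cost is a few sentences. Urine toxicology and timeline follow-back are already scheduled at each of these visits, so no new data are needed. Table 1's Aim 1 sample sizes stand, since they already assume no loss for non-abstinence. The change does not require altering the status of the abstainer analysis within Aim 2, which is a separate question.
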